## Methods/design

### Study design

The D-SCOPE frailty program concerns a Randomized Controlled Trial (RCT). The RCT will compare usual care with an intervention that include tailored care and support and long-term care follow-up. Figure 1 presents an overview of the study design. The D-SCOPE frailty program will start with targeted case-finding, which refers to the selections from the census records based on eligibility criteria [29]. Older adults will receive an invitation letter explaining the purpose of the study, the way on which the study will be conducted and the expectations towards people who agree to participate. A trained volunteer or a researcher will contact them in person and will inform them face to face about the study. Participants will also receive the informed consent form and a letter for the general practitioner explaining the D-SCOPE frailty program. Respondents will have the opportunity to ask questions if anything would remain unclear. Older adults willing to participate will undergo the baseline assessment (T0) after signing the informed consent.

**Fig. 1 Fig1:**
[figure not shown]
Flow diagram of the D-SCOPE frailty program

Older adults who are at least mild frail on one of the 5 domains of frailty (CFAI-plus) or feel frail based on the subjective assessment of frailty will be randomly assigned to either (1) the experimental group or (2) the control group. Older adults with no-to-low frailty (CFAI-plus) or who do not feel frail (subjective assessment of frailty) will be grouped into a third group. A fourth group will include frail older adults willing to participate in the T0 and T1 assessment but not in the intervention part. All groups except for the experimental group will receive care as usual.

All older participants will be assessed after a 6 months’ period. The study will include an effect evaluation and a process evaluation of the RCT. The effect study will be conducted using a quantitative evaluation of the outcome measures for frail community-dwelling older adults. The process evaluation will be performed by a quantitative monitoring of the experimental group (including follow-up telephone interviews) and qualitative focus groups with older adults, informal caregivers and municipal health and social care professionals in each municipality.

The baseline assessment T0 will begin in June 2017 until October 2017. The study assessment T1 will begin in December 2017 until April 2018. The intervention will take place between June 2017 and March 2018, between the baseline assessment T0 and the study assessment T1. The qualitative evaluation will take place in March and April 2018. The data analysis will take place between April 2018 and June 2018.

The content of the program has been developed in close collaboration with representatives of different home care and support levels, i.e. general practitioners, home care organizations, social service of the municipalities, home nurses, older people’s organizations, centers of expertise in housing and care, care insurances companies, universities, etc.

### Setting

The RCT will be conducted in three municipalities in Flanders (Belgium): Knokke-Heist, Ghent and Tienen (*N* = 900, 300 in each municipality). Each municipality was chosen due to their specific characteristics (Table 1). First, the municipalities differ in terms of socio-economic environment [43]. Knokke-Heist is defined as a coastal town, Ghent as a big city and Tienen as a medium-sized town. Second, demographically and regarding welfare and health, Knokke-Heist has been confronted with a sharp increase of older adults despite a low number of places in residential care and a low number of informal care and home care. Like Knokke-Heist, Tienen has more older adults (both 65+ and 80+) than the percentage of the Flemish region. Finally, the population in Ghent has a lower average income in comparison with the Flemish average.

**Table 1 Tab1:** Characteristics of the 3 localities [74–76]

	Knokke-Heist [74]	Ghent [75]	Tienen [76]	Flemish region [74–76]
Demographic data (2016)				
Total number of inhabitants	33,311	257,029	34,185	6,477,804
Population growth since 2005	98.5	111.3	107.7	107.2
Total number of older inhabitants	11,310	42,706	7,243	1,265,666
Older population growth since 2005	128.5	102.1	111.2	117.9
% older adults (65 years and over)	34.0%	16.6%	21.2%	19.5%
% older adults (80 years and over)	9.9%	5.5%	6.5%	5.9%
Socio-economic data (2013)				
Average income per capita in €	23,374	17,477	18,479	18,163
Welfare and health data				
Number of places in residential care in 2016 per 1000 older adults (>65y)	58	84.6	90.2	76
Number of entitled informal and home care in 2015 per 1000 older adults (>65y)	56.3	69	132.1	98.2

### Ethics

This study protocol was reviewed and approved by the medical ethics committee of the Vrije Universiteit Brussel, Brussels, Belgium (reference number: B.U.N. 143,201,630,458). Prior to the baseline assessment and start of the intervention in the experimental group, written consent will be obtained from all participants.

### Participants and eligibility criteria

Study participants will be community-dwelling older adults aged 60 years and over. In order to explore the most efficient selection strategy to detect frail older adults, two randomized selections, with replacement addresses, from the census records will take place in each municipality. Each randomized selection in each municipality will include 150 participants. The two stratified samples will be based on previous research on risk profiles for frailty [29]**.** Risk characteristics for frailty are gender, age, marital status, moved in the past 10 years and migration background. In the first sample (*n* = 450) older participants will need to fulfill at least one criterion. This implies that the participants will be women or aged 70 years and over or not have a partner or have moved in the past 10 years or will have a migration background. In the second sample (*n* = 450) all older participants will need to fulfill all selection criteria. This implies that older participants will be aged 70 years and over, have no partner, and moved last 10 years. The second sample will exclude the variable migration background due to too small samples within the three selected municipalities.

Exclusion criteria will be current hospitalization, institutionalization, when the older participant himself or his/her informal caregiver indicates that the older participant is not able to participate or if the interviewer notes that the older participant is cognitively not capable to provide adequate answers.

Older adults will be included in the RCT if they are at least mild frail on one of the 5 domains of the CFAI-plus (i.e., ≥ 25 for physical frailty, ≥ 12.52 for cognitive frailty, ≥ 20 for psychological frailty, ≥ 37.5 for social frailty and ≥ 5 for environmental frailty) or feel frail based on the subjective assessment of frailty (i.e. at least agree with the statement), and accept to participate in the intervention.

### Randomization

Eligible participants will be randomly assigned directly after the baseline assessment by the principal researcher, using computer-generated randomization to either the control or the experimental group.

### Intervention

The intervention contains several steps in order to empower older adults and improving their access to care and support [28]. Older participants assigned to the experimental group after the first home visit containing the T0 baseline assessment will be contacted by a professional from the social service of the municipality for a second home visit. These professionals will already be experienced with conducting home visits and will receive training and instructions concerning multidimensional frailty, frailty-balance and taking into account the strengths and competences of older adults and their informal caregivers. During the second home visit, the professional from the social service of the municipality will further explore the older adult’s competences, needs and preferences. Based on the results of the baseline assessment and on the results of the second home visit, the professional from the social service of the municipality will propose a type of intervention. The decision and organization of tailored care and support will be made together with the older participant and his/her environment. The older participant will be accompanied in the referral once decided in which organization/form of intervention the older participant will participate in order to reduce dropout. The older participant will receive tailored care and support whereby his competences, strengths and resources will be supported [30]. The intervention will depend on the availability of the care and support services in the municipality, and could be formal (e.g., home care) or informal (e.g., activities of an older adult’s association). A professional from the social service of the municipality will monitor which care the participant receives, when the older person cancels the care and support and if everything is going according to his/her wishes. This will be done monthly by telephone.

### Measurements

Table 2 presents the outcomes of the effect and process evaluation.

**Table 2 Tab2:** SPIRIT diagram outlining schedule of enrolment, intervention and assessments for study participants

Time points		Enrolment	Baseline assessment T0	Intervention	Quantitative monitoring	Monthly follow-up	Study assessment T1	Qualitative evaluation
Introduction/preparation	Screening eligibility criteria	x						
	Information letter	x						
	Informed consent	x						
Study groups	Experimental group		x	x	x	x	x	x
	Control group		x				x	x
	Care avoiders		x				x	x
	Group ≤ mild frail (CFAI-plus) or do not feel frail (subjective assessment of frailty)		x				x	x
	Informal caregivers							x
	Municipal health and social care professionals							x
Primary outcome measures	Quality of life		x				x	
	Meaning in life		x				x	
	Life satisfaction		x				x	
	Mastery		x				x	
	Community inclusion		x				x	
	Ageing well in place		x				x	
Secondary outcome measures	Multidimensional frailty		x				x	
	Physical phenotype of frailty		x				x	
	Feeling frail		x				x	
	Resilience		x				x	
	Coping		x				x	
	Help needed for activities in daily life		x				x	
	Informal and formal care		x				x	
	Medical care		x				x	
	Leisure time		x				x	
	Neighborhood		x				x	
	Future perspective		x				x	
	Life events		x				x	
Additional variables	Socio-demographic variables		x				x	
	Socio-economic situation		x				x	
Process measures	Amount of intended target group that participated in the second home visit/started the intervention				x			
	Amount and types of delivered intervention(s)				x			
	Number refuses, dropouts and completions				x			
	Logbook				x			
	Reasons for refusal/dropout					x		
	Satisfaction of intervention					x		
	Satisfaction D-SCOPE frailty program							x
	Experiences care/support processes							x
	Components that support or inhibit the implementing process of the D-SCOPE frailty program							x

### Effect evaluation

#### Primary outcome measures

The primary outcomes of the effect evaluation will be quality of life, meaning in life, life satisfaction, mastery, community inclusion and ageing well in place.

*Quality of life* will be measured by the use of one item from the abbreviated version of the World Health Organization Quality of Life (WHOQOL-BREF) [44]. *Meaning in life* will be evaluated with the Meaning in Life Questionnaire (MLQ) and will assess perceived meaning in life by the use of 5 items [45]. *Life satisfaction* will be measured by using the Satisfaction with Life Scale, a validated scale which measures global life satisfaction [46]. To assess *mastery*, a questionnaire which evaluates to what extent people feel they exert control over existing circumstances of their lives with 4 items will be used [47]. In addition, one self-constructed item will assess mastery in relation to others [48]. *Community inclusion* will be measured by using 1 item from the Community Integration Measure (CIM) and will ask the participants to what extent they feel like part of the community [49]. *Ageing well in place* will be assessed using a self-constructed question and will explore to what extent the older participant feels he/she lives at home in a qualitative way. Older participants will also be asked to rate the outcomes quality of life, meaning in life, autonomy and community inclusion on a scale from 0 to 10.

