#### Power analysis

As we have no clear view yet on all aspects, factors, scales, outcomes, statistical analyses, etc., it is not feasible to run detailed power analyses a priori. However, according to Cohen [64] and when using the online a priori sample size calculator for independent sample t-tests [65]; the minimum sample size per group (experimental as well as control group) with a probability level of .05, an anticipated Cohen’s d effect size of 0.5 (medium) and a desired statistical power of 0.8 will be 64. To find differences with a small effect size (cohen’s d = 0.2) between the 2 groups a total n of 788 (394 in each group) is required.

As is our longitudinal design is concerned, we have based our a priori estimation on a study of Fabricotti et al. [66]. They expect a 10% loss to follow up (due to mortality, re-housing, impossibility or unwillingness to participate further) between T0 and T1. By including 220 older adults in both the experimental and control group, they state that their sample is sufficient to detect changes. Assuming an average effect size of 0.5 and significance of 5%, this gives a power of 0.997. They further argue that if a small effect size is expected of 0.3 with a significance of 5%, this still supplies sufficient power at 0.837. Interfering variables will also play a role. At an average effect size (f2) of 0.15 and significance of 5%, assuming five independent variables, the power is 0.97. Even with 15 independent variables, the power remains sufficient at 0.856.

So, in sum, it was decided to aim for 900 community-dwelling older adults aged 60 years, equally divided over the municipalities Knokke-Heist, Ghent and Tienen in Flanders, Belgium; so 300 community-dwelling older adults will participate in each municipality.

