### Analysis of the data

#### Effect evaluation

The experimental and control groups will be described at both time points with descriptive statistics. Similarity of characteristics between the two groups will be assessed by means of independent sample t-tests or chi-square tests. Differences in measurements between T0 and T1 will be assessed by means of repeated measures ANOVA’s. In order to explore which combination of resources lead to a higher quality of life, meaning in life, life satisfaction, mastery, community inclusion and ageing well in place in frail community-dwelling older adults, different interaction models with balancing factors as moderators will be tested. We will explore which balancing factors are moderators for having a good quality of life, meaning in life, life satisfaction, mastery, community inclusion and ageing well in place, despite being frail. We will explore the hypothesis that frail older adults who have the adequate resources (positive frailty-balance) have a better chance for aforementioned positive outcomes than frail older adults with a negative frailty-balance. For each measure, regression analyses will be performed with the T1 scores as the dependent variable, the research group (experimental vs. control) as independent variable of interest, and demographic variables and differences in baseline characteristics as co-variates. Multivariate analyses will be performed in order to answer the research questions.

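### Six unranked primary outcomes are analysed separately with no stated success rule, while the sample size allows for a single test at .05

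*Protocol article*

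**What the plan says.** - **Primary outcomes.** Primary outcome measures reads: "The primary outcomes of the effect evaluation will be quality of life, meaning in life, life satisfaction, mastery, community inclusion", with ageing well in place as the sixth. Table 2 lists the same six under the primary heading. Neither place ranks them or names a key outcome.
- **Duplicate measures.** The same section adds that participants will also "rate the outcomes quality of life, meaning in life, autonomy and community inclusion on a scale from 0 to 10". On mastery, beyond a four-item questionnaire, it says: "In addition, one self-constructed item will assess mastery in relation to others". It does not say whether this item is scored with the four-item scale, or which version of a doubly measured construct is the primary one.
- **Analysis.** Under Analysis of the data, Effect evaluation: "For each measure, regression analyses will be performed with the T1 scores as the dependent variable". Repeated measures ANOVA is also planned for T0 to T1 differences. A closing sentence promises multivariate analyses without defining them. No significance level, hierarchy or success rule is given there.
- **Sample size.** Power analysis uses a calculator for independent-sample t-tests "with a probability level of .05". For the medium effect it gives an "effect size of 0.5 (medium) and a desired statistical power of 0.8 will be 64" per group. For d = 0.2, "between the 2 groups a total n of 788 (394 in each group) is required". The same section says there is not yet a clear view of outcomes and analyses.

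**The concern.** The protocol treats six outcomes as equally primary but sizes the trial as if there were one comparison. Without a success rule, a reader of the results cannot tell what one significant primary outcome out of six is worth. Taken as evidence that the programme works, it carries a false-positive risk well above 5%. Where a construct is measured in two ways and neither is named as primary, the more favourable version can be chosen after the data are seen. If the six outcomes are protected against this, the stated group sizes no longer give the intended 80% power for each.

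**Working it through.** **Inputs from the protocol article:** six primary outcomes; alpha .05 (Power analysis only; sidedness not stated); power 0.8; d = 0.5 with 64 per group; d = 0.2 with 394 per group. From the study cited in Power analysis: 220 per group, 10% loss, d = 0.3, power 0.837.

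**Assumptions:** each of the six is tested two-sided at .05; any one significant result counts as success; test statistics share a common correlation, which the document does not give, so a range is shown.

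**1. Reproduce the stated sample size.** Normal approximation: n per group = 2(z₀.₉₇₅ + z₀.₈)² / d².
- d = 0.5: 2(1.960 + 0.842)² / 0.25 = 62.8, so 63. The exact noncentral t gives 63.77, so **64**, as stated.
- d = 0.2: 2(1.960 + 0.842)² / 0.04 = 392.5, so 393. The noncentral t gives 393.4, so **394**, as stated.
- One-sided tests would give 51 and 310, which do not match.

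The stated figures are therefore those of one two-sided test at .05, with no allowance for six.

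**2. Chance of at least one false positive among six.** Under independence: 1 − (1 − 0.05)⁶ = 1 − 0.735 = **0.265**. With a common correlation, by simulation of 400,000 draws of six equicorrelated standard normals, counting draws in which the largest absolute value exceeds 1.96:

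| Assumed correlation | Six tests |
|---|---|
| 0 | 0.265 |
| 0.3 | 0.241 |
| 0.5 | 0.207 |
| 0.7 | 0.164 |
| 0.9 | 0.108 |

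**3. Upper reading.** If the four 0-10 ratings were also tested at primary level (6 + 4 = 10): 1 − 0.95¹⁰ = 0.401 under independence, and 0.351, 0.289, 0.214 and 0.127 at the same four correlations.

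**4. Power at the first Holm step.** Alpha = 0.05 / 6 = 0.00833, two-sided noncentral t, noncentrality d√(n/2):

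| n per group | d | Noncentrality | Power at .05 | Power at .05/6 |
|---|---|---|---|---|
| 64 | 0.5 | 0.5√32 = 2.83 | 0.80 | 0.56 |
| 394 | 0.2 | 0.2√197 = 2.81 | 0.80 | 0.56 |
| 198 | 0.3 | 0.3√99 = 2.98 | 0.85 | 0.63 |

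The 198 is 220 × 0.9, both figures taken from the cited study. The 0.846 computed at .05 is close to the 0.837 quoted from it.

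**5. Size needed for 80% power at .05/6.** 99 per group (d = 0.5), 271 (d = 0.3), 608 (d = 0.2). The last is 1,216 in total, above the planned 900, which also covers the two non-randomised groups.

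**6. The opposite rule.** If all six had to succeed, each with 80% power, joint power under independence is 0.8⁶ = 0.26, and higher with positive correlation. The unstated rule therefore decides what the sample can deliver.

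**The case against.** Several stronger readings are tempting, and the document does not support them.

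- **That four of the six primaries are rated twice.** Only quality of life, meaning in life and community inclusion are. The fourth rating is of autonomy, which is on neither list of primaries. The Discussion names autonomy and omits mastery among the expected benefits, but nothing in the text equates the two.
- **That the plan tests each outcome at 5%.** The analysis section states no level; .05 appears only in Power analysis. Applying it to each outcome is an inference.
- **That there are ten or eleven primary tests.** The protocol counts six. It never calls the ratings separate primary endpoints, nor says that the extra mastery item is scored alone. The ten-test figures are an upper reading only.
- **That one significant result suffices.** The document does not say so. If all six must succeed, the any-one-of-six error rate does not apply. If each outcome is reported strictly as its own claim, a familywise rate is arguably not the relevant one.
- **That 198 per arm is this trial's number.** It is borrowed. The article gives no planned number randomised per arm, and its 900 spans four groups.

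Two further points deserve weight. The multivariate sentence could be meant as a joint test, but it defines none. A multiplicity procedure may also sit in an analysis plan that is not shown, so its absence from an article is not in itself a fault.

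What survives is narrower but solid. The choice of primaries, their measures and the basis of the sample size are protocol decisions. All three are made here, and they do not fit together.

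**Conclusion.** The concern holds in this form: six co-equal primary outcomes, separate regressions, no stated success rule, and a sample size that reproduces only for a single two-sided test at .05. For three primaries and mastery, the version that counts is not fixed.

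Under the two assumptions of testing each at .05 and accepting any one as success, the error rate is about five times nominal under independence (26%) and still about double at a correlation of 0.9 (11%). These figures show the range that the plan leaves open. They are not the error rate of a rule that the protocol states. The mismatch with the single-test sample size does not depend on the correlation. This should be corrected, although part of the answer may already lie in an analysis plan not shown.

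**What to change.** 1. Name one measure per construct as primary: the questionnaire scale or item. Make the four 0-10 ratings and the extra mastery item secondary.
2. Test the six primary outcomes by the Holm procedure at a familywise 5%. It is valid whatever the correlation between outcomes. Other procedures would also serve, provided that one is fixed in advance.
3. Report secondary and moderator results with confidence intervals, as exploratory.
4. Restate power at the first Holm step (.05/6), and say that the 220 per group and 10% loss are borrowed.

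**Cost.** No new data are needed and no added enrolment is proposed. The price is power. For each outcome, it lies between the first-step value and the unadjusted one: 0.56 to 0.80 at 64 per group (d = 0.5) or 394 per group (d = 0.2), and 0.63 to 0.85 at 198 per group (d = 0.3). Where that falls short of the 0.8 target, the protocol should say so.
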